## Background

Antipsychotic drug treatment in patients with schizophrenia is complicated by poor compliance (= adherence to drug prescription) and treatment persistence (= proportion of patients remaining in treatment within a defined time period). It is unclear whether this is caused by the frequent occurrence of adverse drug reactions, varying treatment effect, or due to poor disease insight and treatment motivation, but presumably it is a combination of different factors.

Compliance is important for both disease prognosis, relapse prevention and admission rate (1, 2). Like treatment persistence, it is used as an overall clinical outcome measure for the tolerability and effectiveness of antipsychotics in psychiatric research (3). In recent years, research has focused on both pharmacological and non-pharmacological (psychosocial) interventions that improve treatment persistence and compliance and thus the clinical treatment course in this patient population.

Psychotropic drugs are usually dosed individually according to the observed treatment effect and adverse drug reactions. A large proportion of antipsychotic drugs and drugs used as antipsychotic adjuvants are metabolized by Cytochrome P450 2D6 and 2C19 (CYP2D6 and CYP2C19). Both enzymes are coded by genes that exhibit genetic polymorphism. Genetic polymorphism results in significant variability of drug metabolism and drug concentration. 5 - 10% of the Caucasian population have a CYP2D6 genotype that is associated with reduced enzyme activity (poor metabolizer (PM)) compared to normal (extensive metabolizers (EM)), while approx. 1% have a significantly increased enzyme activity (ultra-rapid metabolizers (UM)). For CYP 2C19, the proportion of PMs is approx. 2-3% (4). It is well documented that PMs achieve significantly higher drug concentrations (5) and have an increased risk of developing adverse drug reactions (7-9), while UMs risk treatment failure (6). A health economic study in psychiatric patients shows that PM and UM status is associated with increased health care costs compared to normal metabolizers (10). This has led to considerations whether CYP2D6 and 2C19 genotyping (CYP test) could lead to an individualized and more tolerable psychotropic drug treatment and should be used routinely (5, 11, 12). However, drug concentrations within one genotype group may vary significantly. Clearly, the CYP genotype is not the only factor influencing drug concentration and tolerability (13). Furthermore, unintended negative consequence of the routine-use of the CYP test, such as decreased clinical observation of adverse drug reactions in patients with normal CYP genotype, cannot be ruled out.

The implementation of early intervention services has shown that nonpharmacological interventions, such as an intensified treatment alliance between patient and psychiatrist affects drug treatment positively. Patients treated by early intervention teams received on average 20% less antipsychotic drugs than those who received usual treatment in psychiatric outpatient clinics. At the same time, patients had fewer psychotic

symptoms and fewer admission days (14). Furthermore, The National Indicator Project has shown that the majority of patients with schizophrenia suffers from adverse drug reactions (15). At the same time, there are major differences in quality and comprehensiveness of adverse drug reaction registration. Thus, in only 23% of cases, sexual side effects were recorded. Therefore, we presume that increased focus on a regular and structured record of adverse drug reactions and effectiveness involving the patient's perception of drug treatment can lead to an improved treatment alliance and influence drug compliance and treatment persistence, drug tolerability and effectiveness.

There are currently no controlled clinical trials comparing genotype guided antipsychotic drug treatment with the clinically guided drug treatment.

## **Purpose**

- To investigate whether CYP test guided treatment improves antipsychotic drug treatment in patients with schizophrenia compared to clinical dose titration.
- To investigate whether intensified clinical monitoring focusing on tolerability, effectiveness and patient's perception of medical treatment can improve antipsychotic drug treatment in patients with schizophrenia compared to control.
- To compare the effect of CYP test guided treatment and intensified clinical monitoring on antipsychotic drug treatment in patients with schizophrenia.

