## **Study Population**

300 patients diagnosed within the schizophrenic spectrum, defined as disorders within the F2 spectrum of ICD-10 (16); 60 extreme metabolizers (PM or UM for CYP2D6 or CYP2C19) and 240 normal metabolizers (EM or intermediate metabolizers (IM) for CYP2D6 or CYP2C19).

The sample size calculation is based on the need to make statistically sound comparisons between the smallest subgroup of the study population, i.e. extreme metabolizers. The calculation is based on the primary outcome "time to discontinuation of initial antipsychotic treatment". Based on the literature, we estimated the smallest relevant difference (d0) to be 45 days and the standard deviation of this parameter to be 39.3. With a type-1 error of 5% and a type 2 error of 10%, n is calculated from the formula:  $n_1 = n_2 = n_3 = 2 \cdot (t_{2\alpha} + t_{2\beta})^2 \cdot \frac{\sigma^2}{d_0^2}$

SD / d0^2 = 19.5, i.e. 20 extreme metabolizers in each study arm. Assuming a prevalence of 10%, approximately 600 patients must be screened to identify 60 extreme metabolizers.

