## **Primary outcome measures:**

- a. Time to discontinue of initial antipsychotic drug treatment.
- b. Persistence for treatment, i.e. percentage of patients remaining in treatment within a defined time period

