#### Recruitment, randomization

Study participants are recruited among patients who are affiliated with the outpatient clinics in the Capital Region. After informed consent, patients are genotyped for CYP2D6 and 2C19. Following primary stratification according to the genotype and use of antipsychotic depot preparations, patients are randomized to one out of three study arms or exclusion from the study. Inclusion continues until there are 20 extreme metabolizers are included in each study arm. Based on an expected frequency of 10% poor metabolizers, a total of 600 patients needs to be screened, of which 100 (20 extreme and 80 normal metabolizers) are included in each study arm and 300 are randomly excluded.

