#### **Data recording**

Immediately after the inclusion, the following information is recorded:

- Demographic data (age, gender, weight and height)
- History of the disease
- Symptom score (SAPS score)
- Side effect score (Udvalg af kliniske undersøgelser (UKU) score)
- Medical history (current and historical)
- Compliance (ROMI)

The following information is registered 12 months after study conclusion:

- Symptom score (SAPS score)
- Side effect score (Udvalg af klinisk undersøgelser (UKU) score)
- Compliance (ROMI)
- Weight

- Metabolic functions (plasma cholesterol, fasting blood glucose, plasma triglyceride, plasma prolactin (only when available in PEM))

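### Time to discontinuation of the 'initial' antipsychotic has no time origin in patients who may be at any point of treatment, and its comparison is planned without adjustment for time already on the drug

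*Protocol*

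**What the plan says.** The Purpose section sets the first aim: "To investigate whether CYP test guided treatment improves antipsychotic drug treatment in patients with schizophrenia compared to clinical dose titration". On the source of patients, the section Recruitment, randomization says "Study participants are recruited among patients who are affiliated with the outpatient clinics in the Capital Region". The inclusion and exclusion criteria cover age, capacity, consent, an F2 diagnosis and no earlier CYP test. None concerns a new start, a recent switch or time on the current drug. Randomization is stratified by genotype and depot use.

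The first primary outcome is "Time to discontinue of initial antipsychotic drug treatment". Neither that section nor the sample size paragraph under Study Population says which drug counts as initial in a patient already on treatment, or when the clock starts. Data processing plans Mann-Whitney, chi-squared and log rank tests, with ANOVA for continuous data. It names no covariate, and its only subgroups are extreme and normal metabolizers. Among the items recorded at inclusion is "Medical history (current and historical").

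**The concern.** For a patient who starts a first antipsychotic on the day of randomization, the outcome needs no further definition. For a patient from the running caseload, *initial* has at least four readings:

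- the first antipsychotic ever taken;
- the drug in use at inclusion, timed from its first prescription;
- the drug in use at inclusion, timed from randomization;
- the first drug chosen after randomization.

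Under the first, the event may have happened before randomization. Under the second, the time includes a stretch that no arm could influence. Only the last two give a quantity that lies wholly after randomization.

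Even with the clock at randomization, someone in the first weeks on a drug and someone on it for years may differ in their chance of stopping within 12 months. If so, pooling them without adjustment adds avoidable noise to the outcome on which the trial is sized, in a comparison with 20 extreme metabolizers per arm. It also leaves a reader unsure which patients the result describes.

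**Working it through.** **1. The plan's own figure.** Inputs from Study Population: "smallest relevant difference (d0) to be 45 days and the standard deviation of this parameter to be 39.3", a type I error of 5% (two-sided) and a type II error of 10%.

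- SD²/d0² = 39.3²/45² = 0.763
- n = 2 × (1.960 + 1.282)² × 0.763 = 16.03, so 17 per arm. With iterated t quantiles it is 17.07, so 18.

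The protocol gives 19.5, "i.e. 20 extreme metabolizers in each study arm". The 19.5 is not reproduced, but 20 is the larger number and gives about 95% power at the stated inputs, so the mismatch does no harm here. The calculation contains no term for treatment phase.

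**2. Inputs the documents do not give.** The share of recent starters and the discontinuation rates by phase are not stated. For illustration only, I assume 12-month discontinuation p = 0.65 in recent starters and p = 0.25 in established users, exponential times, and a share f of recent starters of 10%, 20% or 40%.

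**3. Mean time on drug over 365 days from randomization.** With λ = −ln(1 − p)/365, the restricted mean is p/λ.

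- Recent starters: 365λ = 1.050; mean = 365 × 0.65/1.050 = 226 days
- Established users: 365λ = 0.288; mean = 365 × 0.25/0.288 = 317 days
- Gap between phases: 91 days

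**4. Share of variance due to phase.** The within-phase variance is 2[p/λ² − 365(1 − p)/λ] − mean², which gives 17,240 (recent) and 9,621 (established). The between-phase variance is f(1 − f) × 91.2². The last column is √(2 × between/20), the chance shift in an arm difference with 20 per arm.

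| f | Within | Between | Share due to phase | SD of chance shift, 20 per arm |
|---|---|---|---|---|
| 10% | 10,383 | 749 | 7% | 9 days |
| 20% | 11,145 | 1,331 | 11% | 12 days |
| 40% | 12,669 | 1,996 | 14% | 14 days |

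At f = 20%, full adjustment would lower the standard error of an arm difference from √(2 × 12,476/20) = 35.3 to √(2 × 11,145/20) = 33.4 days. That equals a gain of 1/(1 − 0.107) = 1.12, or 12% more patients. The chance shift of 12 days is about a quarter of the 45-day difference.

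**5. Limits of the illustration.** Its total SD at f = 20% is √12,476 = 112 days, far above the plan's 39.3. It therefore shows direction and rough order, and does not re-estimate the trial's power. The shares apply to mean time on drug. In a Cox model the gain appears as power and not as a narrower interval.

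**The case against.** A reader might infer something stronger: that Purpose 1 contradicts the design, because most patients are already titrated, genotype helps only in an early window, and the effect is therefore diluted. The documents do not support this.

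- *Clinical dose titration* is used for ordinary clinician-led dosing. The Background describes individual dosing by effect and adverse reactions and speaks of clinically guided treatment. The control arm receives usual local practice, and Ethical considerations uses the same phrase for care without the test. Enrolling the clinic caseload fits that pragmatic question.
- Appendix 1 lists observation, serum concentrations, dose change and switching without limiting them to the start of treatment. Drug and dose changes during the study are a secondary outcome.
- No treatment durations are given, so the share of patients past titration, and any selection of those who tolerated their drug, is unknown.
- Dilution figures depend on what is assumed for established users. With a hazard ratio of 0.6 in recent starters, 20% of them in the trial and the rates above, the overall gain is 9 days if established users gain nothing. It is about 16 days if their hazard ratio is 0.8.

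Two further objections have weight. First, chance imbalance in an unstratified factor is ordinary sampling error, which the significance test already allows for. That is correct, and it is why the point concerns precision and not bias. Second, covariates and subgroups are often left to an SAP, which is not shown here. That stands for the absence of a phase subgroup. It does not cover the meaning and time origin of a primary outcome, which belong in the protocol, and the protocol has itself chosen the tests.

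A 12-month study with outcomes recorded at baseline and follow-up suggests that the clock was meant to start at inclusion. That is likely, but the text does not say so.

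**Conclusion.** The point holds in a limited form. The protocol admits patients at any point of treatment, leaves *initial* and its time origin undefined, and names tests that ignore time already on the drug. The arm comparison remains unbiased through randomization. What is lost is precision and a clear reading of whom and what the primary result describes.

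The size cannot be established from the protocol. Under the assumed 65% and 25% discontinuation rates, adjustment would remove roughly 7% to 14% of the outcome variance. If the phases differ less in persistence, the gain is smaller; if they do not differ, there is none. The missing time origin is a defect whatever these values are. Nothing here shows that the effect is diluted or that a null result would fail to answer Purpose 1.

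**What to change.** 1. Under Primary outcome measures, define *initial* as the antipsychotic in use at randomization and start the clock at randomization in all three arms. State how patients on no antipsychotic, or on more than one, are handled, since the entry criteria do not exclude them.
2. Under Data processing, adjust or stratify the time-to-discontinuation comparison for time since start or last change of that drug, for example by Cox regression or a stratified log rank test. With 20 extreme metabolizers per arm, one continuous covariate is easier to carry than further strata on top of genotype and depot use.
3. Show the arm effect by treatment phase as descriptive only.

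Purpose 1 should not be rested on recent starters alone. At shares of 10%, 20% and 40% that would leave about 2, 4 and 8 of the 20 extreme metabolizers per arm.

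The cost is wording and slightly more analysis, with no extra patients and no change in eligibility. The change depends on start dates being captured in the baseline history, which the protocol does not say explicitly. The phase-specific estimates will be imprecise.

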## **Design**

A prospective blinded randomized trial designed as parallel study with three study arms; two intervention arms and one control arm. The study duration is 12 months. Outcome measures are recorded at baseline and 12 months follow up.

## **Study Population**

300 patients diagnosed within the schizophrenic spectrum, defined as disorders within the F2 spectrum of ICD-10 (16); 60 extreme metabolizers (PM or UM for CYP2D6 or CYP2C19) and 240 normal metabolizers (EM or intermediate metabolizers (IM) for CYP2D6 or CYP2C19).

The sample size calculation is based on the need to make statistically sound comparisons between the smallest subgroup of the study population, i.e. extreme metabolizers. The calculation is based on the primary outcome "time to discontinuation of initial antipsychotic treatment". Based on the literature, we estimated the smallest relevant difference (d0) to be 45 days and the standard deviation of this parameter to be 39.3. With a type-1 error of 5% and a type 2 error of 10%, n is calculated from the formula:  $n_1 = n_2 = n_3 = 2 \cdot (t_{2\alpha} + t_{2\beta})^2 \cdot \frac{\sigma^2}{d_0^2}$

SD / d0^2 = 19.5, i.e. 20 extreme metabolizers in each study arm. Assuming a prevalence of 10%, approximately 600 patients must be screened to identify 60 extreme metabolizers.

## **Inclusion criteria**

- Age ≥ 18 years
- Capable of taking care of their own affairs
- Diagnosed with a psychiatric condition within the schizophrenic spectrum (F2, ICD-10) by a specialist in psychiatry
- Able to give informed consent
- Not previously CYP tested

## **Exclusion criteria**

- Previously CYP-tested

## **Primary outcome measures:**

- a. Time to discontinue of initial antipsychotic drug treatment.
- b. Persistence for treatment, i.e. percentage of patients remaining in treatment within a defined time period

## **Secondary effect parameters:**

- a. Compliance. (Participants are categorized as fully, partially or non-compliant based primarily on the patient's own report in a non-judgmental interview. In addition to that, information from serum concentration measurements are collected and patient's understanding of the importance of medical treatment is rated using Rating of Medication Influences (ROMI) scale (18).
- b. Number of drug changes / dose changes
- c. Positive symptoms in schizophrenia (Scale of Assessment of Positive Symptoms (SAPS)) score (17).
- d. Side effect score (Udvalg af Kliniske Undersøgelser (UKU) score) (18), weight, metabolic functions (plasma cholesterol, solid blood sugar, plasma triglyceride, plasma prolactin (only when recorded routinely in the patient's Personal Electronic patient Profile (PEM))
- e. Number and length of admissions during the study period

## **Procedures**

### Training of staff personnel

Prior to the study start, the staff of the outpatient clinics in the Capital Region and other relevant project personnel is offered a training program. The training program includes registration of adverse drug reaction registration by means of an abbreviated version of the UKU (18), systematic questioning of psychotic symptoms using selected parts of SAPS (17) and the use of selected parts of an interview to elucidate the patient's understanding of the importance of medical treatment, Rating of Medication Influences (ROMI) (19). It also includes guidance on how the CYP test result can be used to direct psychopharmacological treatment (Appendix 1).

#### Recruitment, randomization

Study participants are recruited among patients who are affiliated with the outpatient clinics in the Capital Region. After informed consent, patients are genotyped for CYP2D6 and 2C19. Following primary stratification according to the genotype and use of antipsychotic depot preparations, patients are randomized to one out of three study arms or exclusion from the study. Inclusion continues until there are 20 extreme metabolizers are included in each study arm. Based on an expected frequency of 10% poor metabolizers, a total of 600 patients needs to be screened, of which 100 (20 extreme and 80 normal metabolizers) are included in each study arm and 300 are randomly excluded.

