### **Data processing**

Data comparisons are made both between the two study arms, but also between the subgroups of extreme and normal metabolizers in each study arm. Due to the unpaired and presumably nonparametric character of our data, we plan to use Mann-Whitney's rank sum test, chi squared test and log rank test hypothesis testing. For continuous data, ANOVA is used. The level of significance is 5%. Since the selected power measurements are interdependent, it is not necessary to correct for the risk of mass significance.

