#### **Project organization and finances**

The project was initiated by [name], [name] and [name] and received financial support from The Danish National Board of Health and TRYG Fonden. There is no financial link between researchers and private companies, foundations, etc., with interests in the outcome of the research project in question.

All funding is administered by the Finance Department, Bispebjerg University Hospital and used for salaries and administrative expenses. No money is paid to patients participating in the trial.

The project is part of a Medical Technology Assessment (HTA), an interdisciplinary assessment of the clinical,

237 economic and socio-cultural effects of a routine use of the genetic test in psychiatry. The project is a  
238 collaboration between the Clinical Pharmacological Unit and Psychiatric Department E at the Bispebjerg  
239 University Hospital, Copenhagen, the Research Institute of Biological Psychiatry at the Sct. Hans Hospital in  
240 Roskilde and the Danish Health Institute (DSI) in Copenhagen.  
241

242

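### Each arm is enriched to 20% extreme metabolizers against an assumed 10% in the clinics, and the whole-arm comparison names no weighting, so a pooled effect of CYP testing need not describe the clinic population

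*Protocol*

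**What the plan says.** Study Population sets the sample at "60 extreme metabolizers (PM or UM for CYP2D6 or CYP2C19) and 240 normal metabolizers", 300 in all, and sizes it on the extreme metabolizers as the smallest subgroup. The screening target follows: "Assuming a prevalence of 10%, approximately 600 patients must be screened to identify 60 extreme metabolizers".

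Recruitment, randomization gives the mechanism. After stratification by genotype and depot use, "patients are randomized to one out of three study arms or exclusion from the study". The result is "of which 100 (20 extreme and 80 normal metabolizers) are included in each study arm and 300 are randomly excluded".

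The first aim under Purpose is "To investigate whether CYP test guided treatment improves antipsychotic drug treatment in patients with schizophrenia compared to clinical dose titration". Project organization and finances places the trial within a technology assessment of the clinical, "economic and socio-cultural effects of a routine use of the genetic test in psychiatry".

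On analysis, Data processing says "Data comparisons are made both between the two study arms" and adds comparisons involving the extreme and normal subgroups within the arms. It names the rank sum, chi-squared and log-rank tests, and ANOVA for continuous data. It mentions neither weighting nor standardization, and it does not limit the overall comparison to the enriched mix.

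**The concern.** The aim and the technology assessment ask what CYP testing does for schizophrenia patients as they present. The trial deliberately holds twice the expected share of the patients in whom the test is most likely to change treatment. A whole-arm comparison averages over the trial mix, so it answers for a population that the stated aim does not name.

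This matters only if the effect differs by genotype, and the protocol gives reason to expect that. Appendix 1 leaves normal metabolizers on the standard dose with no preference between preparations. For poor and ultra-rapid metabolizers it lists closer observation, serum concentrations, changed doses or a switch. The Background also declines to rule out an adverse effect in patients with a normal genotype, through reduced clinical observation of side effects. The under-sampled group is thus the one in which the protocol itself sees possible harm.

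**Working it through.** **Inputs.** Study Population and Recruitment, randomization: 10% prevalence, 600 screened, 60 extreme and 240 normal metabolizers included, 300 excluded. Study Population: smallest relevant difference of 45 days, used here only as an illustration. Background: CYP2D6 poor metabolizers 5–10%, CYP2D6 ultra-rapid about 1%, CYP2C19 poor metabolizers 2–3%.

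**Step 1: reproduce the plan's figures.** 60 / 0.10 = 600 screened. Normal metabolizers screened: 600 − 60 = 540. Excluded: 540 − 240 = 300, as stated. Sampling fractions are 60/60 = 100% and 240/540 = 44.4%. The extreme share is 60/300 = 20% in the trial and 60/600 = 10% among those screened.

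**Step 2: pooled against clinic effect at 10% prevalence.** Let r be the effect in normal metabolizers divided by the effect in extremes, on a scale where effects average over patients (a mean difference or a difference in percentage persisting). The ratio of pooled to clinic effect is (0.20 + 0.80r) / (0.10 + 0.90r).

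| r | Trial mix | Clinic mix | Ratio |
|---|---|---|---|
| 0 | 0.20 | 0.10 | 2.0 |
| 0.10 | 0.28 | 0.19 | 1.47 |
| 0.25 | 0.40 | 0.325 | 1.23 |
| 0.50 | 0.60 | 0.55 | 1.09 |
| 1 | 1.00 | 1.00 | 1.0 |

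As an illustration, 45 days in extremes and none in normals gives 0.20 × 45 = 9.0 days pooled and 0.10 × 45 = 4.5 days in the clinic mix. The ratio does not depend on the 45.

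**Step 3: other prevalences, with r = 0 and arms still 20:80.** If the two genes are independent, the Background figures combine to 1 − 0.94 × 0.98 = 7.9% at the low end and 1 − 0.89 × 0.97 = 13.7% at the high end. The ratios are 0.20/0.079 = 2.5 and 0.20/0.137 = 1.46, or about 1.5. Simple addition gives 8% and 14%, with ratios of 2.5 and 1.43.

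**Step 4: harm in normal metabolizers.** Suppose extremes gain 45 days and normals lose h days (h is an assumption). The pooled effect is 9 − 0.8h, which is positive while h < 11.25. The clinic effect is 4.5 − 0.9h, which is negative once h > 5. Between 5 and 11.25 days the signs differ. At h = 8 the results are +2.6 and −2.7 days.

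**Step 5: price of standardizing.** Restoring 10:90 weights extremes by 0.10/0.20 = 0.50 and normals by 0.90/0.80 = 1.125, a relative weight of 2.25 = 540/240. With unit variance in both strata, the variance of an arm mean is 0.1²/20 + 0.9²/80 = 0.010625 standardized, against 1/100 = 0.01 unweighted. The ratio is 1.0625, or √1.0625 = 1.03 in standard error.

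**The case against.** The strongest reply is that the protocol states nothing false. It discloses the enrichment and its reason, and weighting is the kind of detail that an analysis plan, not shown here, could supply. Genotype subgroup comparisons are planned, so anyone could recombine the stratum results at any prevalence. The named methods are mainly tests, and the aim asks whether testing improves treatment, not by how many days. The arms are randomized within genotype strata, and with no effect in either stratum the enrichment creates none.

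Much of this stands. There is no bias between arms, the subgroup comparisons are unaffected, and the planned tests can remain. What does not stand is that the matter is only missing detail. The protocol fixes the unequal sampling, fixes the whole-arm comparison and states a broader target. Followed as written, it yields a pooled result for the 20:80 mix, and the subgroup comparisons do not by themselves produce the population-level figure.

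A reader might infer two stronger claims. One is that the overall effect will be overstated twofold. That needs exactly zero effect in normal metabolizers and 10% prevalence; the protocol asserts no zero effect, and the 45 days is a planning difference, not a forecast. The other is that the same error enters the economic assessment. The protocol does not describe that model, which may use genotype-specific effects with population shares.

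**Conclusion.** The point holds as one about the population to which the pooled estimate applies. On the protocol's own numbers the size depends on how far the effect differs by genotype, from no distortion with equal effects to a factor of 2.0 with none in normal metabolizers. At that extreme, uncertainty about prevalence widens the factor to between about 2.5 and 1.5. If testing harmed normal metabolizers, the pooled and clinic effects could differ in sign.

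These figures assume the planned 20:80 arms and an effect measured as a mean difference or a difference in proportions; log-rank statistics and hazard ratios do not scale this way. The point bears mainly on arm 1. It reaches arm 2 only if the effect of intensified monitoring also varies by genotype, for which the protocol gives no reason. Carry-over into the economic assessment is a risk, not something the protocol shows.

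**What to change.** Keep the planned tests for significance. For the all-patients effect, add an estimate standardized to the genotype shares actually observed among screened patients. The planned shares are 10:90, which means weighting normal metabolizers 2.25 relative to extremes. Use a scale on which this is valid: a mean difference, the difference in persistence at 12 months, or weighted survival curves. Use a stratified or robust variance. Averaging stratum-specific hazard ratios is not the same as weighting patients and should not be presented as such.

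If standardization is not wanted, state in Data processing that the pooled result applies to a genotype-enriched 20:80 sample and not to the clinic population.

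The standardized estimate needs counts of screened patients by genotype, a named effect measure and a variance method. No change to recruitment or sample size is needed for it. Its statistical cost is the roughly 6% in variance (3% in standard error) derived above, if variances are equal in the two strata.
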